## Abstract

**Background:**

An important prerequisite for optimal healthcare is a secure, safe and comfortable environment. There is little research on how the physical design of birthing rooms affects labour, birth, childbirth experiences and birthing costs. This protocol outlines the design of a randomised controlled superiority trial (RCT) measuring and comparing effects and experiences of two types of birthing rooms, conducted in one labour ward in Sweden.

**Methods/design:**

Following ethics approval, a study design was developed and tested for feasibility in a pilot study, which led to some important improvements for conducting the study. The main RCT started January 2019 and includes nulliparous women presenting to the labour ward in active, spontaneous labour and who understand either Swedish, Arabic, Somali or English. Those who consent are randomised on a 1:1 ratio to receive care either in a regular room (control group) or in a newly built birthing room designed with a person-centred approach and physical aspects (such as light, silencer, media installation offering programmed nature scenes with sound, bathtub, birth support tools) that are changeable according to a woman’s wishes (intervention group). The primary efficacy endpoint is a composite score of four outcomes: no use of oxytocin for augmentation of labour; spontaneous vaginal births (i.e. no vaginal instrumental birth or caesarean section); normal postpartum blood loss (i.e. bleeding < 1000 ml); and a positive overall childbirth experience (7–10 on a scale of 1–10). To detect a difference in the composite score of 8% between the groups we need 1274 study participants (power of 80% with significance level 0.05). Secondary outcomes include: the four variables in the primary outcome; other physical outcomes of labour and birth; women’s self-reported experiences (the birthing room, childbirth, fear of childbirth, health-related quality of life); and measurement of costs in relation to the hospital stay for mother and neonate. Additionally, an ethnographic study with participant observations will be conducted in both types of birthing rooms.

**Discussion:**

The findings aim to guide the design of birthing rooms that contribute to optimal quality of hospital-based maternity care.

**Trial registration:**

ClinicalTrials.gov NCT03948815. Registered 13 May 2019—retrospectively registered.

## Background

### Introduction to current practice: childbirth care in Sweden

In Sweden, healthcare at birth is offered only at hospitals. The aim of this care is to promote a physiologically normal birth, i.e. where labour starts spontaneously and ends in a vaginal non-instrumental birth, where mothers and babies are healthy and the mothers have a positive childbirth experience [1]. The proportion of physiologically normal births has, however, gradually decreased. By 2018, 21.5% of all births in Sweden were medically induced compared to 7.1% in 1991, and 17.2% of women gave birth through caesarean section (CS), compared to 10.9% in 1991 [2]. Also by 2018, 53.2% of first-time mothers with spontaneous labour received oxytocin infusion for labour augmentation [3]. This high level of intervention in otherwise normal labour warrants increased costs due to increased demands on personnel during the birth itself, prolonged hospital stay, and more frequent readmission in the postnatal period [4]. For example it has been shown to be cost-effective in women with one previous CS to have a vaginal birth on the next pregnancy compared to having a repeat CS [5]. Although a recent trial in the United States has shown a decrease in CS in low risk nulliparous women randomised to have induction of labour at 39 weeks gestation [6], the population comprised women who were predominantly of Hispanic, Asian or African ethnicity (56%), were unemployed (49%) and had obesity (52%). As that population is usually at greater risk of pregnancy and labour complications, and differs considerably from the Swedish population, maternity care in Sweden has not changed practice as a result.

### Existing knowledge on the effect of healthcare environment on health

A secure, safe and comfortable environment is an important prerequisite for providing optimal healthcare [7]. The environment can, however, be experienced differently by patients/clients. A technically sound healthcare facility, for example, provides a sense of security for some people while for others it can create feelings of alienation and a reduced sense of self-determination [8–10]. Thus, for optimal safety, health and efficiency, the care environment should be adaptable enough to meet the unique needs of patients and their companions [11]. Physical design aspects [12] such as single rooms, good ventilation [13, 14], windows [14], conditions that promote orientation and distraction [14, 15], a view of or access to nature, real or artificial [13, 14], and ergonomic furniture [14] can all have positive health effects. Psychological dimensions [12] such as staff with a willingness to help, promotion of integrity, conveying a sense of security and trust through more person-centred care also improve patient/client health [16, 17]. The following aspects contributing to a supportive care environment where it is possible to experience ease have been identified in a tentative theoretical construction: experiencing a genuine welcome; recognising oneself in the space provided; creating and maintaining social relations; experiencing a willingness to be served and cared for; and experiencing safety [16].

### The mechanism of the effect of environment on birth

Labour and birth are innate, biological, instinctive processes that have always been, and still are, linked to certain risks [18, 19]. Therefore, mammalian mothers have instinctively always chosen to give birth in an environment perceived as safe, secure and private [18, 20]. When a woman in labour arrives at the hospital, factors such as loud noise, light and a strange, unfriendly environment increase the activity of some parts of the brain cortex and amygdala that signal danger, and the body’s stress and defence systems are activated. This leads to inhibition of oxytocin release and/or sympathetic nervous system activity may increase. As a result, labour contractions can become too strong and painful, or even cease [18, 20–23], leading to medical intervention [19], such as that seen in the high rate of augmentation of labour with synthetic oxytocin [3]. The opposite also applies; if the cortex and amygdala perceive the environment as safe, harmless, friendly and inviting, this leads to physical and mental relaxation and to decreased fear and stress responses. This leads to more effective labour contractions and to good uterine blood circulation, which positively affect the progress of birth [22, 24], increase oxygenation of the foetus, and prevent postpartum haemorrhage. Touch, warmth and closeness also promote the release of oxytocin and decrease stress levels [25].

Women will remember and be affected by their labour and birth events throughout their lives [26, 27]. Women who feel safe and who can open up to the flow and rhythm of labour can be strengthened [28, 29], but the experience can also leave negative impressions [30]. Non-empathetic treatment by healthcare professionals and threatening or over-medicalised birthing environments can leave negative impressions [31]. A negative experience of birth can cause ill-health in women, such as posttraumatic stress disorder, depression, persistent intense fear of childbirth [31–34], delayed subsequent pregnancy [35, 36] and demands for future operative birth [36, 37].

### Existing knowledge on the effect of healthcare environment on birth

The healthcare environment in relation to birth is inadequately studied. A systematic review by our research group (unpublished), with searches of ten databases in December 2016 and August 2017, showed that birthing rooms that provide comfort using controllable stimuli can provide distraction from labour pain, comfort, control and safety [38] and have positive effects on duration of labour and pain intensity [39, 40]. Sense of familiarity has a positive impact on feelings of control, ownership of space and nest-building behaviours of women and their birthing companions [41–43], while feelings of unfamiliarity distract women when giving birth [44]. These findings clearly suggest that design aspects of a birthing room can influence the outcomes of giving birth and affect women’s decisions about future mode of birth [45]. Our review shows that there is a lack of scientific studies with sufficient quality on the effect of the birthing room itself.

A pilot RCT in Canada found that it was feasible to perform an RCT comparing a more flexible birthing room to a regular one, and that fewer women who had given birth in the flexible birthing room received synthetic oxytocin for augmentation of contractions. The authors recommended a full RCT [46], but at the time of commencement of our planned study no full-scale RCT had been reported. We have found two ongoing RCTs comparing care in a specially designed birthing room with care in a regular room. A single-centre study in Denmark examines whether a birthing room specially designed and decorated to minimise stress has an impact on birth outcomes and the birth experience of the woman and her partner. One of the existing birthing rooms has been rebuilt using a wooden material, home-like non-clinical furniture and a wall projector with nature scenes combined with music and nature sounds. The RCT plans to include 680 nulliparous women at term randomly allocated to either the rebuilt birthing room or the regular birthing room. The primary outcome is augmentation of labour with oxytocin [47]. An ongoing multicenter study in 12 labour wards in Germany will evaluate if a redesigned birthing room that facilitates mobility and upright positioning, coping with pain and personal comfort will result in a higher probability of a vaginal birth in hospital. The environment in the intervention room has been re-conceptualised with special features and equipment, such as a bed hidden from sight by a screen or curtain, a mattress on the floor, foam elements for support, a bean bag and posters depicting upright positions, and a monitor showing nature films with natural sound and music. The study will comprise 3800 women and has vaginal birth as the primary outcome [48].

## Methods/design

Based on the lack of knowledge that was identified concerning the effect and influence of birthing room on the woman and her baby, and the likelihood that maternity wards in some countries will be in need of either reconstruction or new construction of labour wards, we identified the need to conduct a randomised controlled trial (RCT).

This study protocol (version 1, 19th June 2019) is described in accordance with the SPIRIT checklist (Standard Protocol Items: Recommendations for Interventional Trials) [49]. For details see Additional file 1. All major changes to the protocol (e.g. changes to eligibility criteria, outcomes, analyses) will be notified to the trial registry, ethics review board, investigators and participants.

### Aim, hypothesis and study design

The overall purpose of this project is to extend the evidence-based knowledge on the design of birthing rooms and their influence on labour, birth and childbirth experiences in nulliparous women in active, spontaneous labour at ≥ 37 gestational weeks.

The hypothesis has been inspired by and built on the mechanism of the effect of environment on birth [18–25], our own, unpublished systematic literature review, interviews with women some days after having given birth [50], aspects pinpointed by health care professionals at the study hospital and women from a user council (the agency Födelsehuset) information from the pilot study conducted in Canada [46], and from the ongoing study in Denmark [47].

We hypothesise that the physical design aspects of a birthing room have effects on the users (woman, companion and staff), and that users interact with the room and make the space their own by using it and giving meaning to it, making it their place. We also hypothesise that a more adaptable person-centred birthing room may facilitate and enable healthy labour and birth processes and outcomes by reducing stress and facilitating the release of endogenous oxytocin. This will reduce the need for augmentation of labour with exogenous (synthetic) oxytocin, increase the likelihood of a vaginal, spontaneous birth, reduce pathological haemorrhage, increase the occurrence of a positive childbirth experience and reduce fear of childbirth and of giving birth again, without any adverse effects on maternal and neonatal outcomes. We further hypothesise that the added costs of creating a more adaptable person-centred birthing room are compensated for by reduced costs for medical interventions and complications during the hospital stay. Using the more adaptable person-centred birthing room may also give an all-around better experience of the birth process for the woman’s companion and improved job satisfaction for staff, but this has to be, and is planned to be, studied in future projects.

Since the experience and influence of the healthcare environment is personal and complex, its effects have to be studied with objectively measurable methods as well as qualitative methods [7].

Our study is a randomised, controlled unblinded superiority trial (RCT), with two parallel groups comparing the effects of two types of birthing rooms. Care in a regular birthing room will be compared with care in an adaptable birthing room with a person-centred approach (‘new room’). In this new birthing room, the woman can change physical aspects according to her own choices, thus creating an environment with a sense of safety, integrity and familiarity. Various outcomes of labour and birth, women’s self-reported experiences of the birthing room, childbirth and quality of life are measured. Furthermore, costs are compared between the care in the regular room and the new room. An additional ethnographic study will explore the influence and meaning of the birthing rooms (regular rooms and new room) on and for women giving birth.

### Intervention

The study takes place at one of three labour wards at Sahlgrenska University Hospital (SUH), Gothenburg in the west of Sweden. It takes into account a newly renovated birthing room, new technology and education of staff to make best use of the updated facilities.

The labour ward serves women at ≥ 34 weeks of pregnancy. In 2018 the labour ward had 4237 births, where 1372 (32.4%) of the women were nulliparous with a single foetus in cephalic presentation at ≥ 37 weeks with spontaneous start of labour.

All birthing rooms are fully equipped with all necessary medico-technical devices. One of the regular birthing rooms has been reconstructed into a person-centred adaptable birthing room for the intervention group. This room provides the woman with more choices to change it according to her preferences. The main differences between the new room and the regular rooms are described in Table 1.

**Table 1 Tab1:** Main differences between the new room and the regular room

Content	New room	Regular birthing room
Size	23.8 m^2^	19 m^2^
Entrance hall	Yes, 3 m^2^	No
Toilet with shower	Yes	Yes
Bathtub	Yes	No
Window, opening	Yes, hidden if media installation in use	Yes
Lighting	Yes, several options with dimming function	Yes, several options, no dimming
Silencer	Yes, a 40-mm suspended sound absorber in the ceiling	No
Media installation	Yes, installation covers two walls, including the window. Offers choice of programmed nature scenes with light, sound effects and music	No
Birthing bed, ordinary	Yes, covered with homelike bedspread	Yes, no bedspread
Medico technical equipment	Yes, hidden behind a wood-panel wall, which is rolled up when necessary	Yes, fully visible
Rounded corners on furniture	Yes, some	No
Sofa	Yes, can be converted to an extra bed for companion	No
Chair for companion	Yes, designed for comfort, adjustable height	Yes, ordinary model
Mirror	Yes	Yes
Pilates ball	Yes	No
Birth support rope	Yes	No
Cabinet for personal belongings	Yes, with ability to recharge electronic devices such as mobile phone	No

### Recruitment and randomisation of participants

Eligible participants are women ≥ 18 years of age that are classified as “Robson 1”, i.e. nulliparous women at ≥ 37 gestational weeks, with a single live foetus in cephalic presentation, and in spontaneous labour [51]. They should understand either Swedish, English, Arabic or Somali or have access to an interpreter when necessary. When arriving at the labour ward they should be in the active phase of labour as defined in Sweden at the time of study, i.e. two of these three criteria fulfilled: spontaneous rupture of membranes; two or three painful contractions in 10 min; cervix dilated > 3–4 cm or effaced and open ≥ 1 cm. Women with induced labour, planned caesarean section, multiple gestation or in the latent phase of labour will be excluded from the study.

General information about the study is provided to nulliparous women in the antenatal maternity clinics, where most women who give birth at the hospital are cared for. No details about the different types of rooms are given, including no photos. This is to prevent expectations on the part of women or companions who might develop a strong desire to give birth in the specially designed room and then be disappointed if they are allocated to a regular birthing room. It is clarified in the information leaflet that access to the new room is only available through the study and no woman allocated to a regular room can transfer into the new room at any stage.

All nulliparous women arriving at the labour ward are received in either a regular room or a so-called assessment room. The midwife clarifies if the woman is in active labour or not by checking the woman’s contractions, rupture of membranes, pain status, bleeding, fetal position by abdominal palpation and, in most cases, cervical status by vaginal examination. Auscultation of fetal heartbeat with a Pinard’s stetoscope and recording of fetal heartbeat for 20–30 min with cardiotocography is also performed.

If both types of birthing rooms are vacant (i.e. the new room and one of the seven regular rooms), a woman fulfilling the inclusion criteria, and her companion, will be informed about the study orally and by written information, and will be invited to participate. The supplied information comprises:
There are two types of birthing rooms that will be tested in the study, a specially designed room that has increased potential to be adapted to personal wishes and needs, and a regular birthing room.It is only the physical design that differs between the two rooms—the specially designed room will have the same level of medical safety and technology as the regular room.The responsible staff will explain the functions that are available in the room to which the woman will be allocated.

Since the midwife often needs time to clarify if the woman is in active labour or not, randomisation directly at time of arrival is usually not possible. Women who are admitted when the new room or one of the regular birthing rooms are not available will not be included in the study. Women who choose not to participate in the study will not be included in the study. The protocol is applied in exactly the same way for everyone; thus, all women are treated equally.

A woman who wants to participate signs a written consent and is randomised to care in either the new room (intervention group) or to care in one of the regular rooms (control group). The randomisation system is managed by an independent statistician at an agency who has prepared an allocation list based on randomly generated numbers and placed the designated allocation in sequentially numbered, sealed envelopes kept in a study folder only available for staff members at the labour ward. To minimise the risk of detection bias, the woman will at randomisation be provided with the unique four-figured ID code printed on the sealed envelope. The midwife opens the next sealed envelope containing details of the allocation and informs the woman and her partner that they have been allocated to either the new room or the regular room. Blinding of either the attending staff or the participants is not possible. Midwives are not aware of the randomisation sequence and the envelopes are opaque. The independent statistician ensures that the randomisation procedure is followed.

The responsible midwife and other staff will follow the woman to the randomised room and provide care following the same care guidelines in both types of room. The enrollment and flow of the RCT is illustrated in Fig. 1.

**Fig. 1 Fig1:**
[figure not shown]
Flowchart of the Room4Birth randomised controlled trial

Any woman wishing to withdraw from the study, from either group, will be withdrawn immediately. However, without any persuasion from the researchers, she will be asked if she is willing for her data to remain in the database. If she agrees, her data will remain and be analysed with the rest of her allocated group’s data (i.e. intention to treat); if she disagrees, her data will be deleted. If a woman randomised to the new room wants to withdraw from the study at any time, she will be transferred and cared for in a regular room (i.e. standard care in that hospital). If a woman randomised to a regular room wants to withdraw from the study at any time, she will continue to be cared for in that room (i.e. standard care in that hospital).

### Pilot testing

The study was pilot tested during December 2018 to test the study routines, identify and eliminate potential obstacles and simplify the implementation of the study. Before the start of the pilot study the staff at the labour ward received instruction on how to use the facilities in the room and the room was regularly used for the staff to feel comfortable within the environment. After that, nine women fulfilling the inclusion criteria were included in the pilot study. The pilot test showed that the study procedure was feasible; some information sheets were revised to be more understandable and a new checklist was developed to facilitate identification of eligible women. Furthermore, the inclusion criteria further specified that the included woman must be in active labour at enrollment and not spend several hours in a regular room before randomisation since this could affect the experience of the birthing environment negatively.

### Data collection and outcome measures

The primary efficacy endpoint is a composite score measured before discharge from the hospital and compared between the two groups. To ensure holistic data for assessing the effect of the room on labour and birth outcome, both medical and experiential outcomes are included in the score. The composite score is 1 if all the following four parts of the composite variable are fulfilled and 0 otherwise:
No use of synthetic oxytocin for augmentation of labourSpontaneous vaginal births (i.e. no vaginal instrumental birth or CS)Normal postpartum haemorrhage (i.e. bleeding < 1000 ml)A positive overall childbirth experience: 7–10 on a Likert scale with anchor 1 = bad, 10 = good

The secondary efficacy outcomes that will be measured and compared between the two groups are: all four primary variables, body mass index (BMI), gestational week at birth, seeking help for fear of childbirth, mental illness treatment, rupture of membranes, amniotomy, use of synthetic oxytocin for augmentation of labour (duration and highest dose), duration of labour, duration of active labour, use of bathtub, use of epidural anaesthesia, maternal fever during labour, duration of pushing stage, position of woman for vaginal birth, episiotomy, mode of birth (vaginal spontanoeus, vacuum extraction and CS), indication for instrumental vaginal birth and CS, cervical tear, perineal tears divided in grades, postpartum haemorrhage (> 1000 ml), manual removal of placenta, stillbirth, neonatal death during hospital stay, Apgar score at 5 min (1 to 10, and grouped < 4 and < 7), umbilical cord blood samples at birth, sex of newborn, birth weight, skin to skin in the first hour, breastfeeding within first 2 hours, admission to the neonatal unit, and length of mother’s hospital stay. Self-reported experiences and outcomes will be measured 2 h after birth, after discharge, after 3 and 12 months with specific questions concerning experience of the room, childbirth ecperience as a whole, Childbirth Experience Questionnaire (CEQ) [52], Fear of Birth Scale (FOBS) [53], fear of giving birth again [54] and health-related quality of life using the EuroQol 5 Dimension (EQ-5D) health state questionnaire [55]. If the woman does not answer the 3- or 12-month questionnaires she will get up to three reminders once a week, the first two reminders by email followed by one phone text message. Using such techniques in our previous studies resulted in response rates of 70–80%.

*Data entry:* The researchers are blinded to the participants’ responses since the ID code is used during data entry. The woman’s self-reported data will be registered 2 hours after birth (touch screen), and 3 and 12 months after birth (web questionnaire or paper questionnaire). For details see Additional file 2. Data from the medical record will be entered by a research midwife in a web-based form. These data will be double checked. Of the four parts of the primary composite outcomes, the only one that could potentially be swayed is postpartum haemorrhage. To guard against any possibility of bias the following routines are established:
Blood loss will be measured, not estimatedThe same team of midwives will care for women in both arms of the study and for all other women not in the study, so a biased individual will have little opportunity to care for women in the new room very oftenAt least two healthcare personnel will be present at any birth, so both would need to be willing to falsify the results for this to happen, which is unlikely to occur with any frequencyThe researchers make checks on all data and will be on the lookout for any potential anomalies

All electronic data will be kept on a password-protected computer in a locked office at the labour ward for the study. All hard copies of participant details will be kept in a fireproof, locked cabinet for research data at the University of Gothenburg. All data will be stored for 10 years after the end of the study and then securely destroyed.

The healthcare costs related to the hospital stay will be collected from the hospital administrative records. As the study population constitutes only nulliparous women at term without severe increased risks, we assume that adjustments for comorbidity are not needed. A schedule of enrollment, interventions and assessments is presented in Table 2.

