### Statistical methods

All main analyses will be performed on the intention to treat population and followed according to randomisation. The primary analysis and selected secondary efficacy analyses will also be performed on the ‘per protocol’ population. For comparison between the two randomised groups Fisher’s non-parametric permutation test will be used for continuous variables, Mantel-Haenszel Chi^2^ test for ordered categorical variables and Fisher’s exact test for dichotomous variables and Chi^2^ test for non-ordered categorical variables. For dichotomous outcome variables two-sided 95% confidence intervals (CIs) for the difference in proportions between groups will be calculated as well as risk ratios (RRs) with 95% CI. For continuous outcomes two-sided 95% CI for the difference in means between groups will be calculated based on Fisher’s non-parametric permutation test. The main analysis will be the above unadjusted analyses.

We will perform our primary analysis with the composite primary outcome. If group imbalances in important baseline characteristics are found, complementary analyses adjusted for these variables will be performed with analyses of covariance for continuous variables and with generalised linear models with binomial distribution and log link function in order to calculate adjusted RRs with 95% CI for dichotomous variables. The distribution of the variables will be given as mean, standard deviation (SD), median quartiles 1 and 3 (Q1, Q3) for continuous variables and as numbers and percentages for categorical variables. Imputations for missing data will be performed, when applicable. Missing data will be imputed using fully conditional multiple imputation in the main analysis. A sensitivity analysis will be performed with the full analysis dataset without imputation. All tests will be two-sided and conducted at the 5% significance level.

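### Oxytocin dose and duration, pushing time and birth position exist only after events the room is meant to change, so they should be tested only in forms defined for all randomised women

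*Protocol article*

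**What the plan says.** The protocol article introduces a long list under Data collection and outcome measures with "The secondary efficacy outcomes that will be measured and compared between the two groups are". The list includes "use of synthetic oxytocin for augmentation of labour (duration and highest dose), duration of labour, duration of active labour" and "duration of pushing stage, position of woman for vaginal birth, episiotomy". Oxytocin use as yes/no is already covered, because the four components of the primary composite are also secondary outcomes. Dose and duration are therefore additional, quantitative outcomes.

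Statistical methods sets the analysis:

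- Population: "All main analyses will be performed on the intention to treat population and followed according to randomisation".
- Tests: "Fisher’s non-parametric permutation test will be used for continuous variables, Mantel-Haenszel Chi^2^ test for ordered categorical variables", with Fisher's exact test for dichotomous and a Chi-square test for unordered categories.
- Estimate: "For continuous outcomes two-sided 95% CI for the difference in means between groups will be calculated".
- Missing data: fully conditional multiple imputation in the main analysis, where applicable, with a sensitivity analysis without imputation.

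Aim, hypothesis and study design states that the room is expected to reduce augmentation with synthetic oxytocin and to make spontaneous vaginal birth more likely. The article gives no value for a woman without oxytocin, without a pushing stage or without a vaginal birth.

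**The concern.** A woman who received no oxytocin has no infusion time or highest dose unless one is assigned. A woman delivered by caesarean before pushing has no pushing time, and one without a vaginal birth has no position for it. Who falls into these groups is decided after randomisation, by events that the room is meant to influence. If the room works, the users in the two arms are different kinds of women, and so are the women with vaginal births. A difference in means between them mixes any effect of the room with that difference in case mix.

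The plan's general rules, applied to these outcomes without a special provision, lead to one of two results. Either the comparison drops to the subset and is no longer intention to treat, or the blanks count as missing and are imputed, which gives infusion times or birth positions to women who had none.

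At stake is the sign of an outcome close to the trial's proposed mechanism. If the room spares mainly women who would have had short infusions, the remaining users have longer ones on average. The report could then show longer oxytocin exposure in the new room although no woman had more and many had none.

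Labour duration raises a related but different problem. Every participant enters in active labour, so every woman has a duration, but a caesarean ends it early. A shorter mean can therefore reflect more caesareans rather than better progress.

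**Working it through.** The documents give no figure for these outcomes, so there is none to reproduce. The sample size enters only as an input. It does reproduce: 45% v 53%, two-sided 5%, 80% power, continuity-corrected, gives 637 per group, and the exact power of Fisher's test at that size is 80.8%.

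**Inputs from the article.** Control oxytocin use 53.2% (national figure for first-time mothers with spontaneous labour, 2018, in the Background); 637 women per group.

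**Assumed inputs.** The room lowers use by d = 3, 5 or 8 points by sparing the women with least need, and changes nothing for the other users. Need L is standard normal. Infusion time is D = 240 × exp{0.6 × (ρL + √(1−ρ²) e)} min with e an independent standard normal, so the median is 240 min and the log-SD 0.6. The need–duration correlation ρ is 0 to 0.7.

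**Formulas.** A woman is a user if L > c, with c fixed by the proportion of users. Let m = 240 × exp(0.6²/2) = 287.3.

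- Mean among users: m × Φ(0.6ρ − c) / Φ(−c).
- Mean in all randomised women, non-users at 0: m × Φ(0.6ρ − c).

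**Worked case, d = 8 points, ρ = 0.7.**

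- Regular room: c = −0.080; users 287.3 × 0.6916/0.532 = 373.5 min; all women 287.3 × 0.6916 = 198.7 min.
- New room: c = 0.121; users 287.3 × 0.6177/0.452 = 392.7 min; all women 287.3 × 0.6177 = 177.5 min.
- Users only: about +19 min. All randomised: about −21 min.
- Users per arm: 637 × 0.532 = 339 and 637 × 0.452 = 288. The standard error is about 16.9 min, so z = 19.1/16.9 = 1.13.
- Chance of a significant result against the room: 1 − Φ(1.96 − 1.13) ≈ 20%.

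**All scenarios** (simulation of 2,000,000 women; the formulas agree to within simulation error):

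| Fall in use | ρ | Users only, new minus regular (min) | Chance of significant harm result | All randomised, non-users 0 (min) |
|---|---|---|---|---|
| 3 points | 0.3 | +2.7 | 3.6% | −8.4 |
| 3 points | 0.7 | +6.8 | 6.2% | −7.7 |
| 5 points | 0.3 | +4.5 | 4.6% | −14.1 |
| 5 points | 0.7 | +11.6 | 10.4% | −13.1 |
| 8 points | 0.3 | +7.4 | 6.4% | −22.9 |
| 8 points | 0.7 | +19.1 | 20.4% | −21.2 |

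At ρ = 0 the users-only difference is zero, apart from simulation error, and the chance of a harm result is the nominal 2.5%. Highest dose was not simulated, but the same selection applies to it.

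**Pushing time.** Suppose caesareans before pushing fall from a share a to a share b, and the averted women push x minutes longer than the rest. The mean among women who push then shifts by x × (a − b)/(1 − b). With assumed values, 20 × 0.02/0.94 = 0.4 min (8% to 6%) up to 40 × 0.05/0.95 = 2.1 min (10% to 5%), against an assumed mean of 45 min.

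**The case against.** **The restricted analysis is not written down.** This is the strongest point. The article plans intention to treat, and zero is the natural value for a woman who had no oxytocin. Only position is tied to vaginal birth in the text. Denominators may be set in an analysis plan that is not shown. This stands: a reader may infer that a users-only comparison is planned, but the document does not say so. What remains is that the article names these as outcomes to be compared and fixes an estimator and an imputation rule that suit them only with a further provision.

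**Imputation is qualified.** It is to be done only where applicable. A value that cannot exist need not count as missing, so one cannot say that the plan imputes undefined values.

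**Not every listed outcome is affected.** One might extend the point to labour duration and to "cervical tear, perineal tears divided in grades". Labour duration exists for every woman. Tears and episiotomy can be scored as absent after caesarean, and neither tears nor position are compared by means.

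**The size can be overstated.** If the averted users were exactly the lowest 15% in dose (8/53.2), the users' mean would rise by φ(−1.036)/0.85 = 0.27 SD. With a standard error of √(1/339 + 1/288) = 0.080 SD, that is z of about 3.4. It requires dose to follow need perfectly, and nothing in the documents supports that.

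**Labour duration is a weak example.** Assume a mean of 10 h, a log-SD of 0.5 and caesareans falling from 8% to 6%. The mean among vaginal births then rises by 0.1 to 0.2 h, less than its standard error of about 0.3 h (SD 5.3 h, about 590 women per arm).

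**Context helps.** Oxytocin use and mode of birth are reported alongside, so a careful reader could see the change in denominator. That lessens the risk of misreading but does not make the subset test a randomised comparison.

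**Conclusion.** The point holds in a limited form. Oxytocin duration and highest dose, pushing time and position for vaginal birth depend on post-randomisation events that the room is expected to change. Tested among users or vaginal births, they do not give a randomised comparison, and for oxytocin the sign can reverse.

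For infusion time the users-only mean would move about 3 to 19 min against the room while the mean in all randomised women moves about 8 to 23 min in its favour. The chance of a significant false harm result would be 3.6% to 20.4%. These figures rest on assumed infusion times, an assumed fall in use of 3 to 8 points, sparing of the women with least need, and a correlation of 0.3 to 0.7. The bias vanishes at zero correlation and when non-users count as 0. For pushing time it is negligible in size.

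The primary composite is unaffected. A reader might infer that the plan as written will show harm when the room helps; the documents support only that it leaves this open. The change is still worth making before outcome data are compared by arm, because choosing the denominator afterwards could decide the direction of a mechanism-linked result.

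**What to change.** Add a short rule to the analysis plan:

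1. Compare oxytocin duration and highest dose in all randomised women, with non-users set to 0. The planned permutation test and difference in means can be used unchanged.
2. Keep mean labour duration, but complement it with time to vaginal birth, treating caesarean as a competing event. Use times recorded for every woman. The article does not list the time of randomisation as a variable, so check that it is held before making it the starting point.
3. Report users-only and vaginal-birth-only results, including pushing time and position, descriptively by arm and without tests.
4. State that values undefined because the event did not occur are not missing data and are excluded from multiple imputation.

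The cost is some wording and programming, with no new data collection if recorded times are used. The zero-coded mean combines whether oxytocin was used with how much, so it reads less simply than a mean among users. The descriptive subset figures make up for part of that.
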